## Abstract

**Background:**

With the increasing number of non palpable breast carcinomas, the need of a good and reliable localization method increases. Currently the wire guided localization (WGL) is the standard of care in most countries. Radio guided occult lesion localization (ROLL) is a new technique that may improve the oncological outcome, cost effectiveness, patient comfort and cosmetic outcome. However, the studies published hitherto are of poor quality providing less than convincing evidence to change the current standard of care.

The aim of this study is to compare the ROLL technique with the standard of care (WGL) regarding the percentage of tumour free margins, cost effectiveness, patient comfort and cosmetic outcome.

**Methods/design:**

The ROLL trial is a multi center randomized clinical trial. Over a period of 2–3 years 316 patients will be randomized between the ROLL and the WGL technique. With this number, the expected 15% difference in tumour free margins can be detected with a power of 80%. Other endpoints include cosmetic outcome, cost effectiveness, patient (dis)comfort, degree of difficulty of the procedures and the success rate of the sentinel node procedure.

The rationale, study design and planned analyses are described.

**Trial Registration:**

(, study protocol number NCT00539474)

## Background

The early detection of breast malignancies decreases the mortality and morbidity of breast cancer patients. These early-detected tumours are generally small and non-palpable.

Wire Guided Localization (WGL), is currently the most commonly used localization method for non-palpable breast lesions. This technique uses a wire to localize the lesion to be excised. The wire can be inserted under stereotactic or ultrasonographic guidance. WGL has several known disadvantages: the radiologically guided wire placement is technically difficult, particularly in dense breast tissue (the wire can displace and reposition is often restricted because of the hook fixed in the tissue). Surgical excision of a lesion with clear histological margins following wire localization is demanding as well. Finally, patients experience the inserted wire as painful and uncomfortable and there is a small risk of a pneumothorax [1-3].

The Radio Occult Lesion Localization (ROLL) introduced in 1998, is a new technique to localize the non-palpable breast tumour[4]. The ROLL technique utilizes the intratumourally injected radiofarmaceutical that is used for lymphatic mapping and sentinel node biopsy (SNB). In the same surgical procedure, this tracer can be used to localize the primary tumour guided by the gamma probe.

Previous small non randomized trials, comparing WGL and ROLL have found the ROLL technique to be simpler and faster to perform, potentially resulting in fewer costs associated with the use of ultrasound, operation rooms and hospital stay [5].

## Methods/Design

### Design

A multicenter, prospective randomized clinical trial. Eligible patients will be randomized for either radio guided occult lesion localization (ROLL) or wire guided localization (WGL).

### Subjects

Three hundred and sixteen patients will be recruited in 2 years in a University Medical Center and medium sized to large hospitals in the Netherlands.

All patients will have confirmed occult breast cancer (core needle biopsy proven) and need to be treated with a lumpectomy and sentinel node biopsy. Written informed consent will be obtained from all patients. This study has been approved by the ethical board of the university medical center Utrecht.

### Patient selection

All patients will be selected based on the in- and exclusion-criteria. The inclusion of patients will take place at the outpatient clinic in the participating hospitals. Patients will be informed about this trial by both written and oral explanation. Given the number of regular treatments of occult breast tumours in the collaborating hospitals (250–300 patients per year), the aim to finish the inclusion in 2 years is considered realistic.

Women ≥18 years with a non palpable breast carcinoma (cT1) that need to be treated with breast conserving surgery are asked to participate. Exclusion criteria are pregnancy, multifocal tumour growth, in situ ductal carcinoma only, lobular in situ carcinoma only and patients requiring breast amputation.

### Randomization

Randomization is stratified for hospital. In each hospital, randomization within strata is blocked with a fixed block size. Randomization is performed by an independent trial center. If a patient meets the inclusion criteria and has provided informed consent, the physician contacts the trial center by phone. The trial center will perform the randomization of the patients.

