**Figure 1 F1:**
[figure not shown]
Flowchart.

As with all localization techniques, care is required in the initial placement of the lesion marker. A few studies have described failures in placement of the radioactive marker. However, the tracer was positioned correctly in 95–99% of patients[6,7]. After localization, the surgical excision is guided by the probe at its lowest sensitivity setting. The exact site of the lesion can be checked constantly during the procedure by using the probe. In this way centering of the lesion within the specimen can be achieved, potentially resulting in a smaller quantity of removed tissue and a higher chance of achieving tumour free margins.

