### WGL procedure

Patients in the WGL group will receive a guide wire, positioned intratumourally under ultrasonigraphic or stereotactic guidance *after *the scintigrafic imaging 1, 2 or 3 hours post injection. The excision of the tumour is guided by the inserted wire and the sentinel node procedure is performed using per operatively injected patent blue and a gamma probe. This is the current golden standard.

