### Outcome parameters

The outcome parameters are tumour free margins (and number of re-excisions), resection specimen volume, cosmetic outcome, quality of life, cost effectiveness also participating physicians will score the difficulty of the procedures. Patients will be asked to fill in questionnaires on pain during the procedure, quality of life and the cosmetic outcome. A specific burden questionnaire, aimed at evaluating the burden of the cosmetic result, is developed. Such an instrument is currently not available. To further assess the net impact in terms of Health Related Quality of Life (HRQoL) also the EQ5D and the EQVAS will be obtained at T = 0, 6, 12 and 26 weeks after the initial diagnostic work-up.

The outcome of the study can be divided in 3 groups of outcome; negative outcomes, outcomes open to discussion and positive outcomes.

Less tumour free margins in the ROLL group are considered negative outcomes, also more tumour free margins in combination with a larger resection volume is a negative outcome and equal tumour free resection margins combined with larger resection specimens are considered negative. Secondly outcomes open to discussion are more tumour free margins in combination with an equal resection volume and equal resection margins in combination with smaller resection specimens in the ROLL group. Finally positive outcomes are more tumour free resection margins in combination with smaller resection specimens and equal tumour free margins in combination with smaller resection specimens. These data will be based on pathology reports. All surgical specimens will be analysed by one dedicated reference pathologist ([name]).

The overall outcome will be cost-effectiveness in terms of incremental costs per quality adjusted life years gained with a 6 month time horizon. We hypothesize that the short-term burden will result in an overall superior result after ROLL.

When indeed our expectations are evidenced, than a situation of dominance may occur, i.e., costs may be saved while at the same time clinical effects are optimal after ROLL.

Should the results indicate that overall the WGL procedure leads to better clinical outcome a cost-effectiveness analysis is foreseen using bootstrapping to assess the uncertainty with regard to the balance between costs and effects. All analyses will be limited to a half year time horizon. Accordingly, discounting of costs or effects is not applicable.

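### One fixed block size within each hospital, with arms the local team can see, lets a team that knows or infers the size anticipate some allocations

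*Protocol article*

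**What the plan says.** The Randomization section gives the scheme in a few sentences. "Randomization is stratified for hospital", and then: "In each hospital, randomization within strata is blocked with a fixed block size". The size itself is not stated. On procedure: "Randomization is performed by an independent trial center", and "If a patient meets the inclusion criteria and has provided informed consent, the physician contacts the trial center by phone".

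Three other places bear on the point:

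- Patient selection puts recruitment in the same unit that forms the stratum: "The inclusion of patients will take place at the outpatient clinic in the participating hospitals".
- The two procedures look different to those who carry them out. For ROLL, the text after Figure 1 says: "After localization, the surgical excision is guided by the probe at its lowest sensitivity setting". For WGL, the WGL procedure section says: "The excision of the tumour is guided by the inserted wire".
- Under Outcome parameters, "participating physicians will score the difficulty of the procedures", so the physicians know which technique was used.

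The Statistical analysis section provides for multivariate correction if baseline characteristics turn out unbalanced.

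**The concern.** In a block of fixed size with equal allocation, the last places are determined by the earlier ones. This matters when three conditions meet. The people who recruit can see the earlier allocations, their sequence is kept separately from that of other sites, and the block size does not change. Here the article states the second and third directly, and the first follows from the nature of the procedures. A fixed size can also be worked out over successive blocks, because the arms come back into balance at regular intervals.

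The physician decides whom to invite and when to phone. A physician who expects a particular arm next could hold a patient back or not raise the trial with her. There is room for this: Patient selection gives 250–300 treated patients a year, so 500–600 over the two years for 316 places. Between 316/600 = 53% and 316/500 = 63% of that pool need enrol, though some of it may be ineligible.

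If patients were selected in this way, the arms could differ before treatment in ways that affect margins, specimen size, difficulty scores and costs. The Background and Discussion justify the trial by the weakness of non-randomised comparisons, so protecting the allocation is central to its purpose.

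**Working it through.** **Inputs.** Allocation is 1:1 (158 per group, Sample size section), in permuted blocks of one fixed size per hospital (Randomization section). The block size B is not given, so B = 4, 6 and 8 are assumed as a range. The article gives no predictability figure to reproduce.

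**Observer assumed for the fixed-size figures.** The observer knows B and the block boundaries from the first patient and records every local allocation without error. The results are therefore upper bounds.

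**Share of allocations certain in advance.** An allocation is certain once one arm has used up its B/2 places in the block. Over all equally likely arrangements the share is 2/(B + 2):

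- B = 4: 2/6 = 33%
- B = 6: 2/8 = 25%
- B = 8: 2/10 = 20%

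Of 316 patients, that is about 105, 79 or 63 allocations.

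**Share guessed correctly.** The observer always names the arm with more places left and tosses a coin when they are equal. For B = 4, the chances of a correct guess are:

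- place 1: 1/2
- place 2: 2/3
- place 3: (2/3)(1/2) + (1/3)(1) = 2/3
- place 4: 1

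The sum is 2.833, and 2.833/4 = 71%. Full enumeration of all arrangements gives 68% for B = 6 and 67% for B = 8. Chance is 50%.

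**After the change.** Sequences with block sizes drawn at random were simulated (2,000 sequences each, at 40 and 60 patients per hospital; these lengths are assumptions, since recruitment per hospital is not given). The observer knows the possible sizes but not where later blocks begin, and updates the probabilities after each allocation.

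| Scheme | Certain in advance | Guessed correctly |
|---|---|---|
| Fixed 4, size known | 33% | 71% |
| Fixed 6, size known | 25% | 68% |
| Fixed 8, size known | 20% | 67% |
| Random 4/6 | about 6% | about 69% |
| Random 2/4/6 | about 4% | about 70% |
| Random 4/6/8 | about 2% | about 68% |

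Varying the size removes most of the certain predictions. It hardly changes the rate of correct guesses.

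**The case against.** The strongest reply is that the safeguards are better than this concern suggests. An independent center holds the list, and the physician calls only after eligibility and consent. A patient therefore cannot be dropped before consent because of a disclosed assignment. That stands: a reader might infer that concealment has failed, and the document does not support this. What remains is narrower, namely anticipation by someone who follows past allocations and then chooses whom to approach or when to call.

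Second, nothing says that sites know the block size, and neither the number of hospitals nor recruitment per hospital is given. Some allocations would be spent on inferring the size. This also stands, and it is why the percentages are upper bounds and not expected values. Whether the size is disclosed to sites may be settled in the full protocol. The stated choice of a fixed size is what can be criticised here.

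Third, a reader might infer that easier or smaller lesions would be steered to ROLL. Nothing in the article indicates a direction, and eligibility is already limited to non-palpable cT1 tumours without multifocal growth.

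Fourth, it would be too absolute to say that analysis cannot repair the selection. The planned multivariate correction can adjust for a measured factor such as lesion size. It cannot reach an unrecorded judgement about how difficult a case will be.

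The article does not use the word open. That the treating team knows the arm is inferred from the procedures, but the inference is safe.

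**Conclusion.** The point holds as a design weakness that should be changed. It rests on what the article states, a single fixed block size in each hospital, and not on an omission. With visible arms and local recruitment, a team that knows or infers the size can anticipate some allocations despite central telephone randomisation.

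The size of the risk is bounded and not known. At most 33%, 25% or 20% of allocations are certain in advance for blocks of 4, 6 or 8, and at most 71%, 68% or 67% are guessed correctly. These bounds assume 1:1 blocks, a known size and perfect tracking. The document shows an opportunity for selection; it does not show that selection would occur, how large it would be or which arm it would favour. The sample size is unaffected.

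**What to change.** In the Randomization section, replace the fixed block size with block sizes that vary at random within each hospital (for example 4, 6 and 8 in random order), and state that the sizes are held only by the trial center.

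The gain should be described accurately. Certain predictions fall to about 2%, even for an observer who knows the possible sizes, and keeping the sizes undisclosed can only help. The best-guess rate stays near 68%, so a reader should not expect the change to approach 0% certain and 50% guessed. If that remaining guess rate matters, larger blocks or a less restricted method, such as minimisation with a random element, could be considered.

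The cost is a new list at a center that already performs the randomisation. The possible imbalance per hospital is slightly larger: an incomplete final block can leave the arms up to half its size apart, so 4 patients for a block of 8 against 2 for a block of 4.

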### Time schedule

Patient recruitment will take place between 2008 and 2010.

### ROLL procedure

Patients in the ROLL group will undergo intratumoural injection of the radiofarmaceutical under stereotactic or ultrasound guidance. After scintigraphic imaging, 1, 2 or if necessary 3 hours post injection, the excision of the primary tumour and the sentinel node procedure are both guided by a gamma probe. At the site of maximum counts with the gamma probe (Europrobe, Strassbourg, France) patent blue (Bleu patenté V 'Guerbet')is injected intratumourally (see Figure 1).

**Figure 1 F1:**
[figure not shown]
Flowchart.

As with all localization techniques, care is required in the initial placement of the lesion marker. A few studies have described failures in placement of the radioactive marker. However, the tracer was positioned correctly in 95–99% of patients[6,7]. After localization, the surgical excision is guided by the probe at its lowest sensitivity setting. The exact site of the lesion can be checked constantly during the procedure by using the probe. In this way centering of the lesion within the specimen can be achieved, potentially resulting in a smaller quantity of removed tissue and a higher chance of achieving tumour free margins.

### WGL procedure

Patients in the WGL group will receive a guide wire, positioned intratumourally under ultrasonigraphic or stereotactic guidance *after *the scintigrafic imaging 1, 2 or 3 hours post injection. The excision of the tumour is guided by the inserted wire and the sentinel node procedure is performed using per operatively injected patent blue and a gamma probe. This is the current golden standard.

### Outcome parameters

The outcome parameters are tumour free margins (and number of re-excisions), resection specimen volume, cosmetic outcome, quality of life, cost effectiveness also participating physicians will score the difficulty of the procedures. Patients will be asked to fill in questionnaires on pain during the procedure, quality of life and the cosmetic outcome. A specific burden questionnaire, aimed at evaluating the burden of the cosmetic result, is developed. Such an instrument is currently not available. To further assess the net impact in terms of Health Related Quality of Life (HRQoL) also the EQ5D and the EQVAS will be obtained at T = 0, 6, 12 and 26 weeks after the initial diagnostic work-up.

The outcome of the study can be divided in 3 groups of outcome; negative outcomes, outcomes open to discussion and positive outcomes.

Less tumour free margins in the ROLL group are considered negative outcomes, also more tumour free margins in combination with a larger resection volume is a negative outcome and equal tumour free resection margins combined with larger resection specimens are considered negative. Secondly outcomes open to discussion are more tumour free margins in combination with an equal resection volume and equal resection margins in combination with smaller resection specimens in the ROLL group. Finally positive outcomes are more tumour free resection margins in combination with smaller resection specimens and equal tumour free margins in combination with smaller resection specimens. These data will be based on pathology reports. All surgical specimens will be analysed by one dedicated reference pathologist ([name]).

The overall outcome will be cost-effectiveness in terms of incremental costs per quality adjusted life years gained with a 6 month time horizon. We hypothesize that the short-term burden will result in an overall superior result after ROLL.

When indeed our expectations are evidenced, than a situation of dominance may occur, i.e., costs may be saved while at the same time clinical effects are optimal after ROLL.

Should the results indicate that overall the WGL procedure leads to better clinical outcome a cost-effectiveness analysis is foreseen using bootstrapping to assess the uncertainty with regard to the balance between costs and effects. All analyses will be limited to a half year time horizon. Accordingly, discounting of costs or effects is not applicable.

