### Sample size

Sample size is calculated based on the primary endpoint: tumour free margins. Based on currently available literature we assume a difference in tumour free margins of 15% in favor of the ROLL procedure [8-14]. With a statistical power of 80% to detect this 15% improvement as significant (p < 0.05), we will require 158 patients in the control (WGL) group and 158 in the ROLL group.

Assuming a weight of 50 gr in the WGL group and a difference of 10 gr in the ROLL group [15] and a standard deviation of 3 gr, α = 0.05 and β = 0.80, the groups are sufficient to show a significant reduction in weight.

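### The three-way outcome rule gives two verdicts to equal margins with smaller specimens, and none to equal margins with equal volume

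*Protocol article*

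**What the plan says.** Under Outcome parameters the article sets up the scheme: "The outcome of the study can be divided in 3 groups of outcome; negative outcomes, outcomes open to discussion and positive outcomes". It then fills the classes from two axes, tumour-free margins and size of the resection specimen, with ROLL compared against WGL.

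- **Negative:** fewer free margins; more free margins with a larger volume; equal margins with larger specimens.
- **Open to discussion:** more free margins with equal volume; and "equal resection margins in combination with smaller resection specimens in the ROLL group".
- **Positive:** more free margins with smaller specimens; and "equal tumour free margins in combination with smaller resection specimens".

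Under Sample size, margins are the primary endpoint ("Sample size is calculated based on the primary endpoint: tumour free margins"). The planning effect is given as "we assume a difference in tumour free margins of 15% in favor of the ROLL procedure", with 80% power at p < 0.05, so that "we will require 158 patients in the control (WGL) group and 158 in the ROLL group". No control rate is given. Specimen weight has its own planning statement, "Assuming a weight of 50 gr in the WGL group and a difference of 10 gr in the ROLL group", with an SD of 3 g. Under Statistical analysis, the difference in radicality is to be reported with a 95% confidence interval, and specimen weight and size are to be compared by t test.

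**The concern.** A verdict scheme written in advance is useful only if each result leads to one verdict. Here one combination appears in two classes in consecutive sentences, and another appears in none.

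The two verdicts on the repeated combination differ in substance. A positive verdict would support the case for ROLL as a new standard of care that the Discussion sets out; a verdict of open to discussion would not. With both in print, either could be cited as the pre-stated reading once the results are known. The combination is also a natural one for this trial: it arises when the hoped-for margin advantage is not shown but the specimen is smaller.

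**Working it through.** **1. Map the rule onto a grid.** Each verdict in Outcome parameters, placed by margins (rows) and specimen size (columns), ROLL relative to WGL:

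| Free margins | Smaller | Equal | Larger |
|---|---|---|---|
| Fewer | negative | negative | negative |
| Equal | **open to discussion and positive** | **no verdict** | negative |
| More | positive | open to discussion | negative |

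Seven of nine cells have one verdict, one has two and one has none. This needs no calculation.

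**2. Could the two entries mean different things?** One speaks of resection margins, the other of tumour-free margins. The same paragraph also uses a merged form, tumour-free resection margins, for both the equal and the more categories. In each list the companion item concerns tumour-free margins. The wording does not separate the entries, and no other section reconciles them.

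**3. Reproduce the plan's sample size.** With difference d = 0.15, mean rate p̄, and z values 1.960 and 0.842 (two-sided 5%, 80% power):

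n = [1.960·√(2p̄(1−p̄)) + 0.842·√(p₁(1−p₁) + p₂(1−p₂))]² / d²

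- 57% v 72%: n = 159 per group. 58% v 73%: n = 157.
- With a continuity correction, 62% v 77% gives 160 and 63% v 78% gives 157.

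So 158 is attainable, but without a stated control rate it cannot be tied to one pair of rates. A range is used below.

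**4. How often would the doubly classed cell occur?** Assumptions: equal means not significantly different at two-sided 5%; 158 per group; a true weight difference of 10 g; weight stands in for specimen size, because only weight has planning figures.

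*Specimen axis.* With the stated SD, SE = 3·√(2/158) = 0.338 g and 10/0.338 ≈ 29.6, so power is practically 100%. It is still 99% at SD 20 g and 84% at SD 30 g. With the stated SD, the cell's probability is therefore simply the chance of a non-significant margin result, and no assumption about correlation between the endpoints is needed.

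*Margin axis.* SE₀ = √(2p̄(1−p̄)/158) and SE₁ = √((p₁(1−p₁) + p₂(1−p₂))/158). For a positive d, P(non-significant) ≈ Φ((1.960·SE₀ − d)/SE₁), less a lower-tail term that matters only when d is small.

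- 55% v 70%: SE₀ = 0.0545, SE₁ = 0.0538; (0.1068 − 0.15)/0.0538 = −0.80; probability 0.211.
- 74% v 89%: SE₀ = 0.0437, SE₁ = 0.0429; (0.0856 − 0.15)/0.0429 = −1.50; probability 0.067.

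Across control rates from 55% to 74%:

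| True margin advantage | P(equal margins, smaller specimens) |
|---|---|
| 15 points (planned) | 21% to 7% |
| 10 points | 56% to 41% |
| 5 points | 85% to 82% |
| none | 95% |

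The 74% end matches the 89% free-margin rate that the Discussion reports from a non-randomized ROLL series, less 15 points. If the true SD were 30 g and the endpoints independent, these figures would be multiplied by 0.84.

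**The case against.** The scheme can be read as an aid to discussion rather than a formal decision rule: the article says only that outcomes can be so divided. The primary endpoint, its confidence interval, the sample size and the weight comparison are stated separately and do not depend on it. The same section names cost-effectiveness as the overall outcome. The conflict lies between positive and open to discussion, so it cannot turn a negative result into a positive one. All of this stands, and it limits the harm to the interpretation of the result. It does not remove the contradiction, because the article states the scheme in full and an unseen analysis plan does not correct a published rule that disagrees with itself.

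Three stronger readings are tempting and are not supported.

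- A reader might infer that the contradictory result is very likely. Under the planned 15-point advantage it is not: the chance is about 7–21%. It becomes the leading result only if the true advantage is clearly smaller, about 10 points or less.
- A reader might infer from the empty cell that one entry was meant for it. That is possible, but the text does not show which entry, if either, was misplaced.
- A reader might infer that a positive verdict here must rest on non-inferiority of margins. The article gives no non-inferiority margin, so this would be a new criterion and not a reading of the plan.

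**Conclusion.** The rule is wrong as written: equal margins with smaller specimens is both open to discussion and positive, and equal margins with equal volume is unclassed. This rests on the text alone.

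The consequence is an ambiguous pre-stated interpretation of a realistic result on the primary endpoint. The primary analysis itself is sound on this point. The probabilities depend on reading equal as non-significant, on the stated weight difference and SD, and on control rates that the article does not give. They run from about 7–21% under the planned effect to about 95% with no margin difference.

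**What to change.** Before outcome data are seen, reconcile the two sentences. A 3 x 3 table (margins fewer, equal or more; specimen smaller, equal or larger) with exactly one verdict per cell, including equal with equal, would do this.

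State what equal margins means in terms of the planned 95% confidence interval, for instance that the interval includes zero, and give a matching definition for specimen size. The sponsor must choose the verdict for the two defective cells. If the sponsor wants a non-inferiority condition for any cell, a margin has to be stated and justified with it.

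The cost is one table and a sentence of definition. Recruitment, data collection, sample size and the planned tests do not change.

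### Equal margins with smaller specimens is classed both as positive and as open to discussion, and no limit defines equal, so a real margin deficit with ROLL could pass as equal

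*Protocol article*

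**What the plan says.** The protocol article, under Outcome parameters, sorts the possible results into negative, open to discussion and positive.

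- **Negative:** "Less tumour free margins in the ROLL group are considered negative outcomes", whatever the specimen size. More free margins, or equal ones, with larger specimens are negative too.
- **Open to discussion:** "Secondly outcomes open to discussion are more tumour free margins in combination with an equal resection volume", and also "equal resection margins in combination with smaller resection specimens in the ROLL group".
- **Positive:** "Finally positive outcomes are more tumour free resection margins in combination with smaller resection specimens", and also "equal tumour free margins in combination with smaller resection specimens".

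The Sample size section says "Sample size is calculated based on the primary endpoint: tumour free margins", and for the effect "we assume a difference in tumour free margins of 15% in favor of the ROLL procedure", with 158 patients per group. Statistical analysis plans a 95% confidence interval for the difference in radicality and links it to none of the three classes. The Discussion gives superiority as the aim.

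**The concern.** There are two faults in one rule. First, equal margins with smaller specimens appears in two classes, so the label could be chosen after the data are seen. Second, a positive label through that branch rests on a claim of equality, while the design is built to show a difference. Without a limit on how much worse ROLL may be, a comparison that merely fails to reach significance could be taken as equality. What is at stake is the primary, oncological endpoint: a real loss of free margins could be reported as equal and, with smaller specimens, as a success.

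**Working it through.** **The double entry.** "equal resection margins in combination with smaller resection specimens in the ROLL group" (open to discussion) and "equal tumour free margins in combination with smaller resection specimens" (positive) both describe unchanged margins with less tissue removed under ROLL. Nothing in the section separates them.

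**Inputs.** From Sample size: 158 per group, 15 points, 80% power, p < 0.05 (sidedness not stated; two-sided assumed). The WGL free-margin rate is not stated, so I assume three values:
- 57.5%, at which the stated size is reproduced;
- 74%, which is 15 points below the 89% cited in the Discussion for a non-randomised ROLL series;
- 89% itself, as a favourable upper bound.

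**The plan's own figure.** n = [1.96·√(2p̄(1−p̄)) + 0.8416·√(p₁q₁+p₂q₂)]² / 0.15². With 57.5% against 72.5%, p̄ = 0.65: (1.96 × 0.6745 + 0.8416 × 0.6661)² / 0.0225 = 157.5, so 158. The size fits a superiority test at that assumed rate and is not shown to be wrong.

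**Reading A: *equal* means not significant at two-sided 0.05.** For a true deficit d, let SE₀ = √(2p̄(1−p̄)/158) and SE₁ = √((p_C q_C + p_T q_T)/158). Then P(equal) = Φ((1.96·SE₀ − d)/SE₁) − Φ((−1.96·SE₀ − d)/SE₁). Example at 74% against 69%: SE₀ = 0.0508, SE₁ = 0.0507, giving Φ(0.98) − Φ(−2.95) = 0.834.

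**Reading B: *equal or more* means a point estimate no lower than WGL.** P = 1 − Φ(d/SE₁). For the same example: 1 − Φ(0.05/0.0507) = 0.162.

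| Assumed WGL rate | A, 5 points worse | A, 10 points worse | A, 15 points worse | B, 5 points worse | B, 10 points worse |
|---|---|---|---|---|---|
| 57.5% | 85.5% | 57.2% | 23.7% | 18.6% | 3.7% |
| 74% | 83.4% | 51.5% | 19.1% | 16.2% | 2.7% |
| 89% | 74.5% | 32.0% | 6.7% | 9.6% | 0.7% |

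**What reading A lets through.** At about 60% free margins, 95/158 against 78/158 is still not significant: the observed deficit is 10.8 points and the 95% interval reaches 21.7. At about 89%, 141/158 against 129/158 is a deficit of 7.6 points with an interval reaching 15.3. Either interval includes a loss as large as the 15-point gain the trial was sized to find.

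**Power for a claim of not worse, at true equality.** Power = Φ(m/√(2p(1−p)/158) − 1.96) for a limit m. No limit is stated; 5 and 10 points are illustrations.

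| Common rate | m = 5 points | m = 10 points |
|---|---|---|
| 57.5% | 14.4% | 43.6% |
| 74% | 17.2% | 52.6% |
| 89% | 29.5% | 81.1% |

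**The specimen condition.** On the plan's own inputs (10 g difference, SD 3 g), the standard error is 3·√(2/158) = 0.34 g and power is essentially 100%, so this condition would filter out almost nothing. I give no overall probability of a positive verdict: that needs the joint behaviour of margins and specimen size, which is not stated.

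**The case against.** The strongest reply is that this is a condensed article, that the confirmatory claim is superiority, and that the three classes are an interpretive grid and not a test. A fuller document may define *equal*, and the planned interval would show readers any deficit it could not exclude. That tempers the point. It does not remove it, because the grid is printed here, contradicts itself here, and gives a favourable label to a claim the printed sample size was not built to support.

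Several stronger readings are tempting, and the documents do not support them:

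- **That ROLL would be declared positive on equal margins.** The same result is also open to discussion, so the verdict is contradicted, not settled.
- **That specimen size decides and the primary endpoint does not.** Fewer free margins is negative whatever the specimen size, so the endpoint holds a veto. The fair criticism is that the veto has no threshold.
- **That *equal* can only mean not significant.** The text does not say so, and reading B gives much smaller risks.
- **That removing less tissue must raise margin involvement.** The ROLL procedure section argues the reverse: better centring may both spare tissue and help clear the margins.
- **That more free margins with equal volume ought to count as positive.** Asking for benefit on both counts is a choice the sponsor may make.

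**Conclusion.** The point holds in a limited form. One combination sits in two classes, and neither *equal* nor *less* has a limit. The size of the risk depends on a reading the article does not give. On non-significance, a true 5-point deficit is called equal in about 75–86% of trials and a 10-point deficit in about 32–57%. On the point estimate, the figures are about 10–19% and 1–4%. All rest on normal approximations, 158 analysed per group, a two-sided 0.05 level and assumed WGL rates of 57.5–89%; under reading A the risk falls as that rate rises but stays material. With 158 per group the trial has low power to show ROLL not worse within 5 points (about 14–30%). For 10 points it has about 44–81%, depending on the rate.

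**What to change.** 1. Place equal margins with smaller specimens in one class only.
2. Replace *equal* by a rule on the interval already planned: margins count as not worse only if the lower 95% limit for ROLL minus WGL lies above a limit that the sponsor states and justifies in advance.
3. Treat an interval containing both zero and that limit as inconclusive, under open to discussion. State in the same place what counts as *less*.
4. Give the power of this claim at 158 per group, with the WGL rate assumed.

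The cost is protocol wording, with no added patients. The downside is that a positive verdict through this branch becomes harder to reach. Should the sponsor want 80% power for it (one-sided 0.025, true equality, common rates from 60% to 89%), a 10-point limit would need 377 down to 154 per group and a 5-point limit 1507 down to 615. That is a separate decision, which this correction does not require.
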